#### 8.4 Serious adverse events (SAEs)

A serious adverse event is any untoward medical occurrence or effect that

- results in death;
- is life threatening (at the time of the event);
- requires hospitalisation or prolongation of existing inpatients' hospitalisation;
- results in persistent or significant disability or incapacity;
- Any other important medical event that did not result in any of the outcomes listed above due to medical or surgical intervention but could have, based upon appropriate judgement by the investigator.

An elective hospital admission will not be considered as a serious adverse event.

The investigator will report all SAEs to the sponsor without undue delay after obtaining knowledge of the events. Patients in the ICU and MC are critically ill and therefore more prone to SAEs. ICU mortality in the Netherlands is approximately 8.4%. Thirty-five percent of the patients are in need for vasopressor therapy, and 46% of the patients are mechanically ventilated. Furthermore, the National Intensive Care Evaluation Report of 2018 reports that the mean ICU admittance duration is 3 days with a mean in hospital admittance duration of 13 days. Around 75% of the total ICU patients have a low APACHE IV score, and therefore a mortality chance of less than 30%. Thus, SAEs in relation to underlying disease and expected SAEs during the ICU course will not be reported.

The coordinating investigator will report the SAEs through the web portal *ToetsingOnline* to the accredited METC that approved the protocol, within 7 days of first knowledge for SAEs that result in death or are life threatening followed by a period of maximum of 8 days to complete the initial preliminary report. All other SAEs will be reported within a period of maximum 15 days after the sponsor has first knowledge of the serious adverse events.

#### 8.5 Suspected unexpected serious adverse reactions (SUSARs)

Adverse reactions are all untoward and unintended responses to an investigational product (in this case the ALA patch as part of the mitoPO2 measurement) related to any dose administered. No SUSARs of the ALA patch are reported. Therefore, no SUSARs are expected during this study.

Unexpected adverse reactions are SUSARs if the following three conditions are met:

1. the event must be serious (see chapter 7.4);
2. there must be a certain degree of probability that the event is a harmful and an undesirable reaction to the ALA patch, regardless of the administered dose;
3. the adverse reaction must be unexpected, that is to say, the nature and severity of the adverse reaction are not in agreement with the product information as recorded in:
  - Summary of Product Characteristics (SPC) for the COMET device;

- Investigator's Brochure for the ALA patch.

The coordinating investigator of LUMC will report expedited the following SUSARs through the web portal *ToetsingOnline* to the METC:

- SUSARs that have arisen in the clinical study that was assessed by the METC;
- SUSARs that have arisen in other clinical studies of the same sponsor and with the same medicinal product, and that could have consequences for the safety of the subjects involved in the clinical study that was assessed by the METC.

The remaining SUSARs are recorded in an overview list (line-listing) that will be submitted once every half year to the METC. This line-listing provides an overview of all SUSARs from the ALA patch, accompanied by a brief report highlighting the main points of concern.

The expedited reporting of SUSARs through the web portal *ToetsingOnline* is sufficient as notification to the competent authority.

The expedited reporting will occur not later than 15 days after the sponsor has first knowledge of the adverse reactions. For fatal or life threatening cases the term will be maximal 7 days for a preliminary report with another 8 days for completion of the report.

The coordinating investigator of LUMC is responsible for documentation of the SUSAR in the report and *ToetsingOnline.nl*. The principal investigators in the participating centres will inform the coordinating investigator in <24 hours after the occurrence of the SUSAR. In the case of occurrence of 2 or more SUSARs in 6 months' time, the study team will discuss possible termination of the study.

## 8.6 Annual safety report

In addition to the expedited reporting of SUSARs, the coordinating investigator will submit, once a year throughout the clinical study, a safety report to the accredited METC. This will be combined with the annual progress report.

This safety report consists of:

- a list of all suspected (unexpected or expected) serious adverse reactions, along with an aggregated summary table of all reported serious adverse reactions, ordered by organ system.
- a report concerning the safety of the subjects, consisting of a complete safety analysis and an evaluation of the balance between the efficacy and the harmfulness of the ALA patch.

## 8.7 Follow-up of adverse events

All AEs will be followed until they have abated, or until a stable situation has been reached. Depending on the event, follow up may require additional tests or medical procedures as indicated,

and/or referral to the general physician or a medical specialist. SAEs need to be reported until end of study within the Netherlands, as defined in the protocol

### 8.8 Data Safety Monitoring Board

This is a moderate risk study in which the side effect of ALA are well described. The side effects are based on studies with photodynamic therapy. Since the total lightload in photodynamic therapy is significantly higher and longer than during the measurements in this study, no SAEs and SUSARs are expected. Indeed, studies using the ALA plaster for mitoPO2 measurement in Rotterdam reported no serious adverse events and no SUSARs. These studies were performed on healthy volunteers, surgical patients and patients with chronic anaemia. However, these studies reported local side effects of the ALA plaster consisting of erythema, pruritus and transient hyperpigmentation. All these effects were temporary and disappeared mostly within 1-2 weeks' time. No local side effects or other adverse events were seen in our pilot study. To ensure the safety of our study participants, monitoring will take place during the study. Furthermore, the inclusion and exclusion criteria are optimised to minimize the risk for participants. Since safety is an important of our study, we will have attention for AEs, SAEs and SUSARs. With an independent expert on data safety monitoring board confirming the needlessness of a DSMB for the INOX ICU-2 study, no DSMB was initiated for this study either.

## 9. Statistical analysis

### 9.1 Primary study outcome

The primary endpoint is the between- and within-subject variability of mitoPO2 measurements using the COMET measurement system at various moments during a 24 hour period with offset ALA-patches in healthy volunteers and neurosurgical ICU/MC patients to describe the variance mitoPO2 measurements and the effect of time-since-application of the ALA-patch and critical care interventions. Between-subject variability is defined as the variation of mitoPO2 at each measurement time point over the whole group. A mean of the mitoPO2 measurements and the standard deviation (SD) is calculated. This SD represents the between-subject variability. Within-subject variability is defined as the variation of mitoPO2 within one subject at each measurement time point. At each timepoint multiple measurements are taken. Since a mean mitoPO2 at each timepoint is used, the standard deviation (SD) of this measurement per participant is calculated. The mean of this SD of the study population represents the within-subject variability. These will be taken separately per ALA-patch.

### 9.2 Secondary study outcomes

Secondary study outcomes include:

- Description of between- and within-subject variability in healthy volunteers and neurosurgical patients in relation to the between- and within-subject variability of the INOX ICU-2 pilot study (P16.303)
- Report on adverse and serious adverse events of the mitoPO2 measurements.

### 9.3 Statistical methods to be employed

Descriptive statistics will be used to describe the characteristics of the study population. The mitoPO2 at the different time points will be described with means, standard deviations (SD), medians and interquartile ranges (IQR) (Q1/Q3) as appropriate. For each time point, for each patient, a mean of 5 measurements of mitoPO2 is calculated with a corresponding SD. The mean of these standard deviations will be used to calculate the within-subject variability and the standard deviation of the overall mean per time-point will be used to calculate the between-subject variability.

Normality of variable distribution will be inspected using histograms. Assuming normal distribution of variables, the p values of a paired samples t-test will be reported for comparing overlapping measurement moments between patch 1 and patch 2. If variables are not normally distributed a Wilcoxon signed ranked test will be performed.

Signal quality of the mitoPO2 measurement will be described using the mean and SD of the signal quality. The statistical analysis will be conducted using the SPSS (Statistical Package for the Social Sciences) statistical package, release 23.0 (SPSS Inc., Chicago, IL) and STATA.

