## 1. Introduction and rationale

Adequate tissue oxygenation is one of the cornerstones of therapy in critical care medicine, which is guided by intensive monitoring. Monitors are used to assess global oxygen delivery and thus the macrocirculation. However, tissue oxygenation is multifactorial and depends not only on the macrocirculation but also on the microcirculation and local cellular oxygen consumption. In critically ill intensive care unit (ICU) or medium care (MC) patients disturbances in the microcirculation may lead to cellular hypoxia. While it is currently possible to monitor cellular oxygenation, these techniques are still in their infancy.

Mik et al. have recently introduced the protoporphyrin IX (PpIX)-triplet state lifetime technique as the first method to measure mitochondrial oxygen tension (mitoPO2) in living cells and tissues. Experimental results have shown mitoPO2's robustness and clinical potential as a parameter for cellular function. Animal research has shown that mitoPO2 is a capable predictor of lactate increase. With the advent of the COMET measurement system, bedside monitoring of mitoPO2 might allow for therapies to be tailored to individual patients.

During the pilot study of the ongoing INOX ICU-2 study an increase in the variation of mitoPO2 results within one subject at each time point (within-subject variability) was observed the longer the 5-aminoulinic acid (ALA)-patch was in place (see appendix 1, table 1). The mean within-subject variability was 3.0 mmHg at baseline (before red blood cell (RBC) transfusion), 3.5 mmHg 2 hours after RBC transfusion and eventually increased to 7.3 mmHg 3 hours after RBC transfusion. Twenty-four hours after RBC transfusion an even higher within-subject variability of 8.7 mmHg was seen. Similarly, the variation over the group at each time point of mitoPO2 measurements (between-subject variability) seemed stable initially, but increased after 2 hours. The mean between-subject variability was 13 mmHg at baseline, 15.7 mmHg in the first hour after transfusion and gradually increased to 28.2 mmHg after 3 hours, up to 42.5 mmHg after 24 hours (see appendix 1, table 1 and figure 1).

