#### 4.4 Sample size calculation

The statistical significance level will be set at the 5% level. The sample size will be calculated to achieve a statistical power of 90%. In the pilot study preceding the INOX ICU 2 study, performed on 20 critically ill patients, the mean within-subject variability at the final timepoint (after 24 hours) was 8.7 mmHg with a standard deviation of 5.67 mmHg. In a stable ICU population, a within-subject variability greater than 4 mmHg will be deemed to be less precise. This is pragmatically chosen based on the initial course of within-subject variability calculated in the first 2 hours of measurements. Therefore, the sample size calculation would be as follows:

$$Z_{\frac{\alpha}{2}} = 1.96 \text{ (two tailed for } p = 0.05\text{)}$$

$$Z_{1-\beta} = 1.28 \text{ (for } \beta = 0.10\text{)}$$

$$\mu = 8.7 \text{ mmHg}$$

$$\mu_0 = 4 \text{ mmHg}$$

$$\sigma = 5.67 \text{ mmHg}$$

$$n = \left( \sigma \frac{Z_{\alpha/2} + Z_{1-\beta}}{\mu - \mu_0} \right)^2 = 15.$$

To allow for an expected 10% dropout rate the corrected sample size will be  $15 \times 1.1 = 17$ . The sample size will therefore be 17 subjects for both groups. The study will first commence in healthy volunteers. The study will continue in neurosurgical patients admitted to the ICU and MC of Leiden University Medical Center postoperatively. In 2018, on average 19 postoperative neurosurgical patients were admitted to the ICU / MC of the LUMC per month. For the period March 2019 – June 2019 (matching the period in which this study is expected to be executed) the average was 17.25 admissions per month. Taking these averages into account, 17 neurosurgical patients has been deemed feasible in the allotted time. Further information on the number of admissions of neurosurgical ICU/MC patients can be found in appendix 4.

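### Between-subject SD is one of two primary components, but section 9.3 gives it no measure of uncertainty and its only test cannot compare such SDs

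*Protocol*

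**What the plan says.** Protocol section 9.1: "The primary endpoint is the between- and within-subject variability of mitoPO 2 measurements using the COMET measurement system". The same section says this is meant to show the effect of time since patch application and of critical care interventions.

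Section 9.3 defines the between-subject part: "the standard deviation of the overall mean per time-point will be used to calculate the between-subject variability". Otherwise it lists means, SDs, medians and interquartile ranges. Its one inferential method is a paired t-test, or a Wilcoxon signed-rank test if the data are not normal, for patch 1 against patch 2 at overlapping moments.

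The Summary and section 2.2 list descriptions of variability between the offset patches and in relation to the INOX ICU-2 pilot; section 9.2 repeats the pilot item. No method is attached to either.

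Section 4.4 sizes the study on the within-subject part. Its inputs are a pilot mean within-subject SD at 24 hours that "was 8.7 mmHg with a standard deviation of 5.67 mmHg" and the rule that "a within-subject variability greater than 4 mmHg will be deemed to be less precise". The result is 15 subjects, raised to 17 per group for dropout.

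On the pilot's between-subject SD, section 1 reports 13 mmHg at baseline, which "gradually increased to 28.2 mmHg after 3 hours, up to 42.5 mmHg after 24 hours".

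**The concern.** An SD from 15 people is an imprecise estimate, and a list of such SDs shows no sign of that imprecision. The reader of the results will be asked whether the between-subject SD rose over 24 hours, differed between patches, differed between volunteers and patients, or differed from the pilot. Without an interval or a method that compares SDs, those questions are settled by eye.

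The paired test does not help. It asks whether the average within-subject difference between patches is zero. Two patches can have the same mean and very different spread across subjects, and the test would not register it.

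This matters most for moderate changes. Sections 1 and 4.1 chose both cohorts to have few disturbing influences, so changes smaller than the pilot's are plausible. A moderate difference could then be reported as a rise, or its absence as stability, when the data cannot separate the two.

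**Working it through.** **Inputs from the protocol.** 15 evaluable and 17 enrolled subjects per group (4.4); 20 pilot patients (4.4); pilot between-subject SDs of 13.0 mmHg before transfusion, 28.2 at 3 hours and 42.5 at 24 hours (Appendix 1, Table 1).

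**Assumptions.** Subject means are normally distributed. The correlation of subject means between two time points or patches is not given in the protocol, so a range of 0 to 0.8 is used.

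**1. The plan's own figure.** n = (5.67 × (1.96 + 1.28) / (8.7 − 4))² = (5.67 × 3.24 / 4.7)² = 15.28, stated as 15. Then 15 × 1.1 = 16.5, stated as 17. This reproduces, and every input is within-subject.

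**2. Precision of one between-subject SD.** The 95% limits are the estimate × √((n−1)/χ²), with χ² at its 97.5% and 2.5% points on n−1 degrees of freedom.
- n = 15: 0.73 to 1.58 times the estimate
- n = 17: 0.74 to 1.52 times the estimate

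**3. Ratio of two SDs in the same 15 subjects, no true change.** Simulated bivariate normal pairs, upper limit of the central 95% range:

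| Assumed correlation | Upper limit |
|---|---|
| 0 | 1.72 |
| 0.3 | 1.68 |
| 0.5 | 1.61 |
| 0.8 | 1.40 |

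At correlation 0 the exact value is √F(0.975; 14, 14) = 1.73.

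**4. Independent groups (patients v volunteers).** The SD ratio that a two-sided 5% F test detects with 80% power is 2.17 for 15 v 15 and 2.06 for 17 v 17. Against the 20 pilot patients, if all contribute at the time point, it is about 2.0 to 2.1.

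**5. Can the planned test see a difference in spread?** Simulated with n = 15, equal means and SDs of 13.0 and 42.5 mmHg, the paired t-test rejects about 5% of the time at every correlation tried. That is its false-positive rate.

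**6. What a suitable paired method would see.** The pilot ratios are 28.2 / 13.0 = 2.17 and 42.5 / 13.0 = 3.27. Pitman-Morgan test, n = 15, two-sided 5%:

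| True change in SD | Power, correlation 0 to 0.8 |
|---|---|
| 1.5-fold | 30% to 64% |
| 13.0 to 28.2 (2.17-fold) | about 80% to 98% |
| 13.0 to 42.5 (3.27-fold) | about 99% or more |

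**The case against.** The best reply is that section 2.2 calls the study descriptive, that no threshold or decision hangs on the between-subject SD, and that interval methods often sit in an analysis plan. Section 11.6 foresees such a plan, and it is not at hand. This has weight: the absence of an interval alone would be a weak point. But section 9.3 does choose a test, and that test cannot serve the comparisons of between-subject SD that the protocol plans. A description of a difference in spread also needs some indication of noise.

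Four stronger readings are tempting and do not hold:

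- A reader might infer that the sentence "The sample size will be calculated to achieve a statistical power of 90" per cent claims power for both halves of the endpoint. Section 4.4 names the within-subject quantity, its time point and its threshold directly afterwards, so the scope can be read from the text.
- A reader might infer that no comparison of between-subject SD is planned. Descriptive comparisons between patches and with the pilot are listed; what is missing is a method able to support them. Nor is the paired test misapplied: the protocol never says that it tests between-subject SD.
- A reader might quote one figure, such as 1.6-fold, as the most that chance can produce. That value is a 95% limit, not a maximum, and holds only near an assumed correlation of 0.5.
- A reader might take the pilot's 2-hour step (13.0 to 20.4 mmHg) as the change at risk. The schedule in section 7.2.1 has no 2-hour measurement, and sections 1 and 7.1.1 tie the design to the rise after 3 hours.

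**Conclusion.** The point holds in a limited form. One of two primary components is to be reported without any statement of uncertainty, and the only named test cannot address it.

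The study is not too small to see what prompted it: a within-cohort rise as large as the pilot's at 3 or 24 hours would usually stand out from chance. The gap lies in changes of about 1.5-fold within a cohort and in contrasts between cohorts or with the pilot, where a ratio of about 2 or more is needed for 80% power. These figures rest on normality and, for paired comparisons, on a correlation that the protocol does not give; marked skewness could make the SDs less stable still. It is a worthwhile, inexpensive improvement to the analysis and does not put the design in doubt.

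**What to change.** In section 9.3:

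- Give a 95% interval for each between-subject SD, by bootstrap over subjects or, if normality is reasonable, by chi-square.
- Compare T0 with T5 within each cohort, and patch 1 with patch 2 at the overlapping moments, by a paired variance method: the Pitman-Morgan test or a bootstrap interval for the SD ratio, resampling subjects.
- Give the SD ratio with its interval for patients against volunteers, and for each cohort against the pilot.
- State that the paired t-test or Wilcoxon test compares levels between patches and does not address between-subject SD.

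Optionally, add one sentence to section 4.4 on the expected precision of the between-subject SD (0.73 to 1.58 times the estimate with 15 subjects).

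The cost is a little more analysis and a few lines of text, with no extra subjects or measurements. The drawback is that the study's stated reach will look more modest.

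### Section 9.3 chooses between the paired t-test and the Wilcoxon test from the normality of the variables, although both tests depend on the paired differences; the effect is small and a change of wording cures it

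*Protocol*

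**What the plan says.** Protocol section 9.3 describes one hypothesis test, the comparison of the two offset patches at the moments when both are measured. The rule has three parts:

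- What is inspected: "Normality of variable distribution will be inspected using histograms".
- If normal: "Assuming normal distribution of variables, the p values of a paired samples t-test will be reported for comparing overlapping measurement moments".
- If not: "If variables are not normally distributed a Wilcoxon signed ranked test will be performed".

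The criterion is normality of the variables each time. Neither section 9.3 nor any other section mentions checking the paired difference. Section 9.3 also says what is derived at each moment: "For each time point, for each patient, a mean of 5 measurements of mitoPO 2 is calculated with a corresponding SD". It does not say whether the mean or the SD is then compared between patches.

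Two pilot figures bear on the point. Section 1 gives the between-subject SD of mitoPO2 as rising "up to 42.5 mmHg after 24 hours", and section 4.4 reports that "the mean within-subject variability at the final timepoint (after 24 hours) was 8.7 mmHg with a standard deviation of 5.67 mmHg". Section 4.4 also fixes the significance level ("The statistical significance level will be set at the 5% level") and arrives at 17 subjects per group.

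**The concern.** A paired t-test is a one-sample t-test on the differences, and the signed-rank test ranks those same differences. Whether the t-test suits the data therefore depends on the shape of the differences. The shape of each patch's own values across subjects is a separate matter, because whatever a subject contributes equally to both patches cancels on subtraction. The two shapes can part in either direction:

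- Values may be skewed between people while the differences are close to normal. The rule then moves to Wilcoxon without need.
- Values may look normal while a few subjects give erratic differences. The rule then keeps the t-test where Wilcoxon would be stronger.

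The pilot makes the second case plausible, since the within-subject SD itself varies strongly between people (mean 8.7, SD 5.67 mmHg). At stake is some power in a secondary comparison with at most 17 pairs per group. The choice of test could also change from one overlap to the next for reasons that have nothing to do with the patches.

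**Working it through.** **1. Sample size (section 4.4).** n = (σ(1.96 + 1.28)/(μ − μ0))² = (5.67 × 3.24/4.7)² = 15.28, stated as 15. Then 15 × 1.1 = 16.5, giving 17. The figure reproduces. It was not derived for the patch comparison, which has no power calculation of its own, so 15 and 17 pairs are used below.

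**2. Number of overlaps (section 7.2.1, Table 2).** On patch 1's clock, patch 2 is measured at 0+3, 1+3, 3+3, 21+3 and 24+3 = 3, 4, 6, 24 and 27 h. Patch 1 is measured at 0, 1, 3, 6, 24 and 27 h. Four moments coincide, and the rule could choose differently at each.

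**3. What the pilot says about the differences.** The noise variance of one five-reading mean at 24 h is (8.7² + 5.67²)/5 = 21.6 mmHg², against 42.5² = 1806 mmHg² for the values: 1.2%. For a difference of two such means it is 2 × 21.6 = 43.1 mmHg². This covers repeat-reading noise at one spot only. The real patch difference also contains site and time-since-application effects, which the protocol does not quantify. With a patch correlation ρ (assumed), SD of the difference = SD × √(2(1 − ρ)):

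| Raw SD (mmHg) | ρ = 0.3 | 0.5 | 0.9 | 0.98 |
|---|---|---|---|---|
| 13 | 15.4 | 13.0 | 5.8 | 2.6 |
| 42.5 | 50.3 | 42.5 | 19.0 | 8.5 |

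The share of the raw variance common to both patches equals ρ, so it is unknown.

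**4. How often each check flags non-normality.** Simulation with n = 17, Shapiro-Wilk at 5% standing in for the histogram, raw SD 20 mmHg and difference SD 3 to 20 mmHg; all shapes are assumed.

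| Raw values | Differences | Flagged on values | Flagged on differences |
|---|---|---|---|
| normal | normal | 7–10% | 4–6% |
| normal | 10% outlier-prone | 6–22% | 47–50% |
| lognormal | normal | 74–78% | 5–6% |

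**5. What a wrong choice costs.** n = 17, true shift 0.75 SD of the differences.

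| Differences | Power, t | Power, Wilcoxon |
|---|---|---|
| normal | 0.83 | 0.79 |
| Laplace | 0.83 | 0.86 |
| t, 3 df | 0.87 | 0.93 |
| 10% outlier-prone | 0.83 | 0.95 |

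Type I error is 0.035 to 0.051 across both tests, at 15 and 17 pairs.

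**6. The whole rule against the same rule applied to the differences.** Mean mitoPO2 is compared; subject SDs are drawn with mean 8.7 and SD 5.67; raw values are normal. An extra patch-to-patch SD is assumed. The shift is 4 mmHg with no extra SD, then kept at the same multiple of the difference SD.

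| Extra SD (mmHg) | Tests disagree | Power, n = 15: rule v differences | Power, n = 17: rule v differences |
|---|---|---|---|
| 0 | 33–36% | 66 v 70% | 71 v 76% |
| 3 | 20–21% | 64 v 66% | 67 v 70% |
| 5 | 16–17% | 61 v 61% | 68 v 69% |
| 10 | 13% | 61 v 61% | 66 v 66% |

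A repeat run with an extra SD of 3 to 10 mmHg gave 12–23% disagreement and losses of about 0.5 to 2 points. With skewed raw values, disagreement was 38–46% and the loss 1 to 3 points. Setting the patch correlation between 0.3 and 0.98 instead gave disagreement of 33–54% with unequal noise (loss 1 to 5 points) and 19–58% with lognormal values and normal differences (loss up to about 2 points).

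**7. If per-subject SDs are compared.** With the same distribution of subject SDs, the rule cost no power.

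**The case against.** The case on the other side has several parts.

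- **Loose wording.** The word variables does not exclude the difference, and an analyst may look at the differences anyway. That is possible, but section 9.3 states a rule, repeats its criterion, and never names the difference. It is a stated rule aimed at the wrong object, and so more than a detail left for the analysis plan.
- **Descriptive study.** The primary outcomes are SDs and no decision hangs on this p value. This stands, and it keeps the point minor.
- **Tested quantity.** The patch objective concerns variability, so per-subject SDs may be what is compared, and then no power is lost. This stands as a limit, since section 9.3 leaves the quantity open.
- **Stand-in.** A histogram judged by eye is not a Shapiro-Wilk test. This stands too: the disagreement rates are indicative only.

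A reader might also infer more than the documents support:

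- *That the histogram shows almost nothing but between-subject spread.* The 1.2% noise share leads there only if reading noise is the sole source of patch differences. The patches sit on separate skin sites and are applied 3 hours apart, and no patch-to-patch SD is given. The 24 h pilot values are also the most extreme ones and come from transfused, critically ill patients.
- *That the power loss is large.* If 15% of subjects are assumed to have differences with SD 25 rather than 5 mmHg and the shift is 5 mmHg, power is 56 v 69% (n = 15) and 59 v 75% (n = 17), losses of 13 and 16 points. Nothing in the protocol supports that contamination or that shift.
- *That false positives increase.* They do not, under either test.

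**Conclusion.** The point holds as a minor fault. The normality rule in section 9.3 is tied to the variables, while the tests it selects depend on the paired differences, so the selection can go wrong in either direction.

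Its size cannot be fixed from the protocol. Starting from the pilot's within-subject figures, with an assumed extra patch-to-patch SD of 0 to 10 mmHg and normal or skewed values, the rule and a check on the differences disagree in roughly 12 to 46% of data sets. The cost is about 0 to 5 percentage points of power. The upper end of the power loss needs reading noise to be the main source of patch differences. Other assumed correlations push disagreement as high as 58% without a larger loss. Type I error stays at or below about 5%. The primary SD estimates and the sample size of 17 per group are unaffected, and there is no power loss if per-subject SDs are compared.

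**What to change.** In section 9.3, make the normality check refer to the paired differences (patch 1 minus patch 2) at each overlapping moment. Use the paired t-test if these are approximately normal and the Wilcoxon signed-rank test otherwise. Alternatively, name one paired test for all overlaps in advance and drop the data-driven switch.

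The first option changes one phrase and needs no new data or subjects. The second has a small price if Wilcoxon is fixed and the differences are in fact normal: about 3 points of power in the setting above (0.83 v 0.79 at n = 17; 0.826 − 0.794 = 0.032 before rounding).

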## 7. Methods

### 7.1 Study procedures

#### 7.1.1 General

The study population will initially consist of healthy volunteers recruited via LUMC notice boards. Subjects will be interviewed prior to participation by a member of the research team, at which time information about the study will be provided and eligibility for participation will be determined based on the inclusion and exclusion criteria. Due to the 'off-label' use of the Alacare patches, specific information pertaining to its current use will be given. A written informed consent will be obtained from all volunteers. Upon inclusion further instructions for ALA-patch application will be provided along with alcohol wipes and 1 ALA-patch.

A self-adhesive ALA-patch will be applied parasternal and a second ALA-patch 3 hours later to rule out influence of the ALA-patch on the measurement variability, while keeping all other possible influencing variables the same. This offset of 3 hours was chosen since an increase in between- and within-subject variability was observed after 3 hours in the INOX ICU-2 pilot study. The course of mitoPO2 measurements will be measured at multiple predefined moments with several overlapping measurements. Subsequently, mitoPO2 measurements will be performed in neurosurgical ICU/MC at multiple predefined moments. This information will be used to further explore the increased variability in the critical care setting where it was first observed.

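### The second patch is meant to rule out a patch influence, but the only inference fixed for the patch comparison is a difference-test p value, which cannot do that

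*Protocol*

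**What the plan says.** Protocol section 7.1.1 (General) gives the purpose of the offset patch: "a second ALA-patch 3 hours later to rule out influence of the ALA-patch on the measurement variability". Section 1 describes the same purpose more softly, as accounting for the influence of the patch.

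Protocol section 9.3 fixes the inference for the comparison: "the p values of a paired samples t-test will be reported for comparing overlapping measurement moments between patch 1 and patch 2". A Wilcoxon signed-rank test replaces it if the variables are not normal. The section names no confidence interval for the paired difference, and it does not say whether the tested variable is mean mitoPO2 or the within-subject SD.

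Other output is planned. Section 9.3 lists means, SDs, medians and interquartile ranges of mitoPO2 per time point, and section 9.1 reports the variability measures separately for each patch. The Summary and section 2.2 word the patch objective as a description.

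Section 4.4 sizes each cohort for a different question, a one-sample comparison of the expected within-subject variability with 4 mmHg. On that limit it says "In a stable ICU population, a within-subject variability greater than 4 mmHg will be deemed to be less precise".

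**The concern.** Ruling out an influence is a claim of absence. A test of no difference can give evidence of a difference. When it is not significant, it shows only that the data are compatible with zero, and they may also be compatible with differences that matter. If the p value is the only inference, the stated purpose of the second patch could be met only by finding p > 0.05. That result becomes more likely as pairs are lost or readings get noisier.

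The offset patch is the design feature that separates the age of the patch from everything else acting on the same subject at the same moment. An over-read non-significant result would weaken the within-subject evidence on whether the patch contributes to the rise in variability seen in the pilot study.

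**Working it through.** **1. The plan's own figure.** Section 4.4 takes "The statistical significance level will be set at the 5% level" (two-sided, z = 1.96), 90% power (z = 1.28), an expected within-subject variability that "was 8.7 mmHg with a standard deviation of 5.67 mmHg", and a reference value of 4 mmHg.

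n = (5.67 × (1.96 + 1.28) / (8.7 − 4))² = (5.67 × 3.24 / 4.7)² = 15.28, given as 15. Then 15 × 1.1 = 16.5, given as 17.

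The figure reproduces. It concerns a one-sample gap of 4.7 mmHg and gives no sizing for the patch comparison.

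**2. Power of the planned test in standardised units.** Two-sided paired t-test at 5%, noncentral t with n − 1 degrees of freedom and noncentrality d√n, where d is the true mean difference divided by the SD of the paired differences:

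| d | 17 pairs | 15 pairs |
|---|---|---|
| 0.4 | 34% | 30% |
| 0.5 | 49% | 44% |
| 0.6 | 64% | 58% |
| 0.8 | 87% | 82% |

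Power of 80% needs d = 0.72 with 17 pairs or 0.78 with 15.

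**3. Width of the interval.** The 95% half-width is t(0.975, n − 1) × SDdiff / √n. With 17 pairs this is 2.120 / √17 × SDdiff = 0.51 × SDdiff. With 15 pairs it is 2.145 / √15 × SDdiff = 0.55 × SDdiff.

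**4. In mmHg of within-subject SD.** The protocol gives neither the SD of the paired differences nor the correlation ρ between patches, so both are assumptions here. With the section 4.4 SD of 5.67 mmHg on each patch, SDdiff = 5.67 × √(2(1 − ρ)). This is 4.0 mmHg at ρ = 0.75, 5.67 mmHg at ρ = 0.5 and 8.0 mmHg at ρ = 0. With 17 pairs, the chance of missing a true difference is:

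| True difference | SDdiff 4 | SDdiff 5.67 | SDdiff 8.0 |
|---|---|---|---|
| 2 mmHg | 51% | 72% | 84% |
| 3 mmHg | 17% | 46% | 69% |
| 4.7 mmHg | 0.5% | 11% | 38% |
| 95% half-width | ±2.1 mmHg | ±2.9 mmHg | ±4.1 mmHg |

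At an SDdiff of 4 to 5.67 mmHg, a non-significant result can therefore sit beside an interval that extends 2 to 3 mmHg or more from zero. For scale, the pilot table in Appendix 1 shows within-subject variability of 3.0 mmHg at baseline and 7.3 mmHg at 180 minutes.

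**5. Can the planned summaries fill the gap?** No. The interval for a paired difference needs the SD of the differences, which depends on ρ. Separate means and SDs for each patch do not supply it.

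**The case against.** The strongest reply is that the comparison is descriptive. The Summary, section 1 and section 2.2 speak of describing, observing or accounting for differences. The phrase about ruling out appears once, under study procedures, and can be read as a reason for the design. Intervals for a secondary comparison are often left to a statistical analysis plan, and one may exist. Much of this stands, and it keeps the point to a mismatch between two statements in the protocol. A descriptive aim also calls for an estimate with its uncertainty, so it does not favour a bare p value.

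A reader might infer three stronger things that the protocol does not support:

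- **That the p value is the only planned output.** Sections 9.1 and 9.3 also plan summaries for each time point and each patch. Only the interval for the difference is absent.
- **That the protocol will treat p > 0.05 as no influence.** No section states such a rule. It is a risk created by the wording of 7.1.1.
- **That any relevant difference is missed about half the time or more.** That holds for about 0.5 SD or less. It fails for 4.7 mmHg, the gap used in section 4.4, which is missed 0.5% to 38% of the time across the SDs shown.

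An equivalence margin of 1 mmHg, taken from the pilot baseline of 3.0 and the limit of 4 mmHg, is also tempting. The protocol does not state one. Every half-width shown exceeds 1 mmHg, so with 17 pairs such a rule would almost never allow a conclusion of no influence.

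Nor would a non-significant test by itself shift the explanation to the ICU setting. The healthy volunteers are followed over time with no ICU exposure, and a rise in variability there would still be informative.

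**Conclusion.** The point holds as a mismatch between sections 7.1.1 and 9.3. The stated purpose is to rule out an influence, and the inference fixed for it can only detect one. With 17 subjects per cohort, or about 15 evaluable, the test is reasonably sensitive to large differences (87% or 82% power at 0.8 SD). It is weak for moderate ones (49% or 44% at 0.5 SD). In mmHg the answer depends on an SD of the paired differences that the protocol does not give, so the miss rates should be quoted only as ranges with that assumption stated.

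The mismatch exists whichever variable is tested. The mmHg figures for within-subject SD apply only if the test is run on that quantity, which section 9.3 leaves open although the aim in 7.1.1 concerns variability.

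**What to change.** In section 9.3, report the mean paired difference (patch 1 minus patch 2) with its 95% confidence interval at each overlapping moment in each cohort, alongside the p value. Where the Wilcoxon test is used, give the median difference with its interval. Do this for the within-subject SD, which the stated aim concerns, as well as for mean mitoPO2. Add that p > 0.05 will not be read as absence of influence.

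In section 7.1.1, replace the wording about ruling out an influence with wording about estimating it. No equivalence margin is then needed. If the sponsor wants to keep the claim, the sponsor must set a margin in advance and judge the interval against it.

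The cost is wording in two sections, with no extra subjects, readings or visits. The downside is that non-significant overlaps will often have to be reported as inconclusive.
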